## Abstract

**Background:**

Subarachnoid hemorrhage is a common and dangerous disease with an unfavorable prognosis. Patients with poor-grade subarachnoid hemorrhage (Hunt & Hess Grades 4–5) are unconscious on admission. Because of the high mortality and disability rate associated with poor-grade subarachnoid hemorrhage, it is often treated conservatively. Timing of surgery for poor-grade aneurysmal subarachnoid hemorrhage is still controversial, therefore this study aims to identify the optimal time to operate on patients admitted in poor clinical condition.

**Methods/design:**

Ninety-nine patients meeting the inclusion criteria were randomly assigned into three treatment groups. The early surgery group received operation within 3 days after onset of subarachnoid hemorrhage (day of SAH = day 1); the intermediate surgery group received operation from days 4 to 7, and surgery was performed on the late surgery group after day 7. Follow-up was performed 1, 3, and 6 months after aneurysm clipping. Primary indicators of outcome included the Extended Glasgow Outcome Scale and the Modified Rankin Scale, while secondary indicators of outcome were assessed using the Barthel Index and mortality.

**Discussion:**

This is the first prospective, single-center, observer-blinded, randomized controlled trial to elucidate optimal timing for surgery in poor-grade subarachnoid hemorrhage patients. The results of this study will be used to direct decisions of surgical intervention in poor-grade subarachnoid hemorrhage, thus improving clinical outcomes for patients.

**Trial registration:**

Chinese Clinical Trial Registry: ChiCTR-TRC-12002917

## Background

Subarachnoid hemorrhage (SAH) is a common fetal cerebrovascular disease. Its annual incidence is 2–32 cases per 100,000 population, and contributes to 5% of stroke cases [1,2]. More than 85% of SAH are caused by aneurysms [3]. Poor grade aneurysmal subarachnoid hemorrhage (PGASAH) , is classified as Grade IV and V and accounts for approximately 20-40% of patients with SAH [4]. The prognosis of PGASAH is extraordinarily poor. More than 60% patients will become dependent or will die [5,6]. Without surgical intervention, the mortality rate of PGASAH can reach more than 90% [7].

Neurosurgical clipping and endovascular coiling are considered two main treatments for patients with intracranial aneurysm. Whether patients with aneurysms can benefit from surgery is still controversial, especially for those with PGASAH, which is the most critical subtype of SAH. In 2003, Maurice-Williams RS asserted the history of aneurysm surgery would end with experienced neurosurgeons is draining away as a result of death and retirement [8]. However, the truth of the matter was quite different.

Previous trials have been performed to compare the prognosis of neurosurgical clipping and endovascular coiling. The most significant study is the International Subarachnoid Aneurysm Trial (ISAT) conducted by Molyneux et al. [9]. Two thousand one hundred forty three patients with aSAH were randomly divided into neurosurgical clipping (n = 1070) or endovascular treatment. Outcomes at 1 year indicated that although the rebleeding rate was more common after endovascular coiling than neurosurgical clipping, endovascular coiling resulted in better clinical outcomes.

However, some flaws existed in the ISAT study. First, optimal timing of surgery may not have been considered, because a 14 hours lapse in the intervention timing of the two treatments. Second, the study excluded more cases that were suitable for neurosurgical clipping. Third, the study didn’t include middle cerebral aneurysms. Fourth, long-term follow-up outcomes were unknown. Fifth, The ISAT study ignored a selection bias, with major surgical intervention centers in the United States and Japan being excluded [10]. Furthermore, the ISAT Collaborative Group distinctly known that the number of patients younger than 40 years or older than 70 years was small, no consistent trend for age was observed. And a limited number of patients with PGASAH were enrolled in the ISAT study [9]. So, the conclusion that patients with aSAH who received endovascular coiling showed a better clinical outcome than those received neurosurgical clipping should be suspected.

The timing of surgical intervention for SAH has been debated worldwide. Pros and cons exist for patients with PGASAH who received different timing of surgery. PGASAH patients are more prone to encounter rebleeding than patients in good clinical condition [11-14]. Early surgery can secure the aneurysm neck to avoid rebleeding which would cause irreparable outcomes, and reduce disability rate and mortality [6]. If the patient receives early surgery, triple-H therapy can be performed as soon as possible to avoid vasospasm postoperatively [14,15]. However, in early surgery, serious cerebral edema may cause brain injury, postoperative hemorrhage, difficult exposure of the aneurysm intraoperatively and other operative complications [16]. The advantages of delayed surgery include the less brain swelling and less cerebrovascular instability during the surgery. Decline in operative mortality have been associated with the operation that is relatively easy. However, the aneurysm may rupture again if surgery is delayed, thus increasing mortality [17].

Surgery timing for patients with PGASAH have the most uncertainty. Previous authors [5,18-21] carried out many researches on the surgery timing of PGASAH, yet a surgery timing still remains unclear. However, till now, only one prospective randomized study has been detected. Ohman et al. randomized 216 patients with SAH in clinical Grades I to III (according to the Hunt & Hess classification) into three operation groups: acute surgery (0 to 3 days after SAH), intermediate surgery (4 to 7 days after SAH), or late surgery (after day 7). At 3 months post-SAH, clinical outcomes indicated that there was no difference in the prognosis of the three groups [18]. In 2002, Ross et al. reported a study enrolled 1168 patients with SAH, and the outcomes indicated that there were no significant difference at discharge or 6 months between the early group (day 1–3), intermediate group (day 4–10) and late group (day 11–21). However, this study was only concerned with the prognosis of surgical patients, ignored the relationship between clinical grades, rebleeding and prognosis [19], the outcomes were widely suspected. Hutchinson et al. [5] reported their study with comparable outcomes, and their study contained similar shortfalls in analysis (as mentioned above). In 2002, de Gans et al. performed a systematic review, where only 11 studies, 1 randomized clinical trial and 10 observational studies, met the inclusion criteria [20]. Meta-analysis showed that outcomes were better after early or intermediate surgery than after late surgery, for patients who were in good clinical condition at admission. For patients in poor clinical condition, results suggest only a trend toward a better outcome for early or intermediate surgery when compared with late surgery. In 2005, Nieuwkamp et al. reported an observational study, which included 411 patients. The study demonstrated that clinical prognosis of patients in poor clinical condition on admission who received early surgery was statistically better than late surgery [21]. It is easy to detect that there is no randomized controlled trial concern about PGASAH.

The controversy over the optimum timing of surgery for patients with PGASAH has continued for many years, and evidence for the optimal timing of surgery in this condition is still insufficient. No randomized controlled trial specifically concerning PGASAH has currently been performed. We designed a trial to evaluate the prognosis of patients with PGASAH receiving surgery at different times, with the aim to identify optimal timing for surgical intervention.

## Methods/design

### Study objective

To compare the efficacy of different timing for surgical intervention in PGASAH. We will also attempt to screen patients with PGASAH who would benefit from surgical intervention.

### Overview of study design

West China hospital receives the most patients with PGASAH in western of China. This study is a prospective, single-centre, observer-blinded, randomized controlled trial with stratification according to the patient’s age, gender, Hunt & Hess grading and the size of aneurysm. Ninety-nine patients meeting the criteria will be randomly assigned into three treatment groups. The early surgery group will receive operation within 3 days after onset of SAH, the intermediate surgery group from days 4 to 7, and the late surgery group after day 7 post-SAH.

### Sample size

The rate of unfavorable outcomes in patients with PGASAH is approximately 50% [22]. A statistically significant difference in unfavorable outcomes between the different surgery times is 30%, which would have statistically significant differences. A sample size of 88 will be required with 80% power and a 5% (2-sided) significance level. On consideration of the loss to follow-up, the sample size will be increased to 99 subjects.

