### Statistical analysis

Intention-to-treat (ITT) analysis and per-protocol (PP) analysis will be performed. The level of significance required for 80% power and a 5% (2-sided) significance level will be used. All data will be analyzed by the statistical analysis using Statistical Package for Social Sciences software (SPSS), version 17.0. Quantitative variables will be analyzed using t-test. Chi-square test and Fisher’s exact test will be used to analyze categorical variables. To analyze the outcome at 6 months after surgery, a comparison between groups will be made using the Mann–Whitney U-test and the significance of observed differences in outcome will be assessed with the Fisher’s exact test. Survival analysis will be further compare mortality between groups. Logistic regression will be used to adjust the effect of multivariable.

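### The 88 patients said to give 80% power fit a two-arm comparison; spread over three arms they give about 57–71% for any one pair

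*Protocol article*

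**What the plan says.** The Sample size section of the protocol article takes an unfavorable-outcome rate of roughly 50% from a cited source and names 30% as the difference of interest between surgery times. It then states: "A sample size of 88 will be required with 80% power and a 5% (2-sided) significance level". The allowance for attrition follows: "On consideration of the loss to follow-up, the sample size will be increased to 99 subjects". The section gives no formula, test, contrast, per-arm number or number of arms, and it does not say whether the 30% is absolute or relative.

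The Overview of study design says: "Ninety-nine patients meeting the criteria will be randomly assigned into three treatment groups". The arms are early, intermediate and late surgery.

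The Statistical analysis section lists chi-square and Fisher's exact tests for categorical variables. For the six-month outcome it names a Mann–Whitney comparison and adds that "the significance of observed differences in outcome will be assessed with the Fisher’s exact test". It also repeats the 80% power figure in the sentence that sets the 5% two-sided level.

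**The concern.** The sample size paragraph compares two rates, while the trial has three groups. If 88 is what a single two-group comparison needs, dividing it by three leaves each pair with about two thirds of the patients that the stated power requires.

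This paragraph is the article's only justification for the size of the trial, and the article says that the results will guide surgical decisions. With 80% power, a non-significant pairwise result would be read as missing a true 30-point difference one time in five. If the real figure is 57–71%, it would be missed about 29–43% of the time, and a null result would carry more weight than it should.

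**Working it through.** **Inputs.** From the Sample size section: reference rate 50%, difference 30%, power 80%, two-sided alpha 5%, 88 patients before losses and 99 after. From the Overview of study design: three arms. Assumptions: the 30% is absolute (50% versus 20%; 50% versus 80% is symmetric), and allocation is equal, since no ratio is stated.

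**Step 1: reproduce 88.** Two routes give it exactly, and both are two-arm totals.
- Fisher's exact test, power by full enumeration, 50% versus 20%: 43 per arm gives 79.6% and 44 per arm gives 80.2%. So 2 × 44 = 88.
- Simple formula, per arm: 2(z₀.₉₇₅ + z₀.₈₀)² × 0.25 / 0.30² = 43.6, rounded up to 44. So 2 × 44 = 88.

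Nearby two-arm methods give 78 (pooled normal approximation, 39 per arm) and 90 (with continuity correction, 45 per arm).

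**Step 2: patients per arm.** The implied loss is 1 − 88/99 = 11.1%. Then 88/3 = 29.3, so the arms hold 29, 29 and 30 evaluable patients. With no losses, 99/3 = 33.

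**Step 3: power for one pair, 50% versus 20%.** Exact enumeration, two-sided 5%, no multiplicity adjustment:

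| Evaluable per arm | Fisher | Chi-square, uncorrected |
|---|---|---|
| 29 v 29 | 57.2% | 67.1% |
| 29 v 30, by which arm has 30 | 62.2–64.7% | 70.0–70.9% |
| 33 v 33 (no losses) | 65.7% | 75.4% |
| 44 v 44 (two-arm design) | 80.2% | 86.4% |

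**Step 4: global test over three groups.** Chi-square with 2 df, noncentral approximation, λ = (N/3) Σ(pᵢ − p̄)² / [p̄(1 − p̄)]. For rates 50/35/20 at N = 88, λ = 29.33 × 0.045 / 0.2275 = 5.80, which gives 57% power.

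| Rates in the three arms | N = 88 | N = 99 |
|---|---|---|
| 65/50/35 | 53% | 58% |
| 50/35/20 | 57% | 62% |
| 50/50/20 | 68% | 73% |
| 50/20/20 | 74% | 79% |

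**Step 5: one arm against the other two pooled.** With about 29 versus 59, power is about 78% with Fisher and 80–83% with chi-square. This is the only binary contrast that comes near the stated figure.

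**Step 6: other readings of the 30%.** Centred on 50% (65% versus 35%), Fisher power at 29 per arm is 53%. As a relative reduction (50% to 35%), it is about 14% with Fisher and about 20% with chi-square.

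**Step 7: difference detectable with 80% power at 29 per arm, downward from 50%.** By chi-square, 33.5 points gives 78.7% and 34 points 80.2%, so about 34 points. By Fisher, 36 points gives 79.0% and 36.5 points 80.6%, so about 36–37 points.

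**The case against.** Four objections deserve an answer.

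- **The origin of 88 is not documented.** This stands. The two-arm reading is inferred from matching numbers. The shortfall does not depend on it, because Steps 3 and 4 use only the stated inputs and the number of arms.
- **A reader might infer that the trial's power is simply 57%.** That is the lowest case: Fisher's test on the one pair with 29 in both arms. The other pairs give 62–65%, and the chi-square test, which the plan also lists, gives 67–71%. Only the range is supported.
- **A reader might infer that no analysis in the plan could reach 80%.** The documents do not support that either. The pooled contrast in Step 5 comes close, although the protocol describes no such contrast and aims to compare the three timings. The primary outcomes are ordinal scales, and a Mann–Whitney comparison is named for six months. Under one illustrative assumption (eight levels, proportional-odds shift from 50% to 20% unfavorable), simulated Mann–Whitney power was about 82% at 29 per arm. That figure depends on an assumed distribution. The Sample size section is built on a binary rate, so it does not vindicate the calculation as written.
- **Multiplicity.** The section claims no familywise control, and an adjustment may sit in an analysis plan that is not shown. No part of this point rests on one.

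That this is a condensed article does not remove the conflict. The article itself gives the rate, difference, power, alpha, total and number of arms, and these do not fit together.

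**Conclusion.** The point holds. For the binary outcome on which the trial is sized, 88 evaluable patients in three equal arms do not give 80% power for a 30-point absolute difference in one pairwise comparison, and neither does a global three-group chi-square test. The pairwise shortfall is about 9 to 23 percentage points at 88 evaluable, and about 5 to 14 if nobody is lost. The conclusion rests on equal allocation and an absolute difference from 50%. The other two readings of the 30% checked in Step 6 give lower power. It does not show that the trial is too small for every analysis it names, or that more patients must be recruited.

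**What to change.** **Sample size section.** Keep 99 patients. Replace the 80% claim with the power that the three-arm design gives for a named comparison and test. For one pairwise comparison of 50% versus 20% at two-sided 5%, without multiplicity adjustment and with 88 evaluable in total, that is about 57–65% with Fisher's exact test, or up to about 71% with the uncorrected chi-square test. State that the 30% is an absolute difference. Add the difference detectable with 80% power at 29 per arm, downward from 50%: about 34 points by chi-square, about 36–37 points by Fisher.

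**Statistical analysis section.** Drop the 80% power wording and keep the 5% two-sided level.

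**Cost.** Wording only, with no extra patients. The stated power becomes less favourable. For orientation, keeping 80% per pair with Fisher would take 3 × 44 = 132 evaluable patients, or 132 / (88/99) = 148.5, so about 149 randomised. The correction does not require this.

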### Inclusion criteria

● Age between 18 to 80 years old.

● Patient diagnosed with a definite subarachnoid hemorrhage, using computed tomography (CT) or lumbar puncture.

● Patient had at least one intracranial aneurysm, detected by DSA, MRA or CT angiography, which was responsible for the recent subarachnoid hemorrhage.

● Patient was in poor neurological condition (Hunt & Hess Grades IV or V) on admission.

● No more than 72 hours from onset to admission.

● According to ethics committee requirements, the person responsible for the patient must agree to participate in this trial and sign the informed consent.

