### Randomization

Minimization, a kind of balance randomization method, will be used in this trial. Characteristics of patients who meet the selection criteria will be submitted to random analyst. After the data is entered into a computer, patients will be randomly divided into an early, intermediate or late surgery group using specialized minimization software. Once random allocation has been determined, groups cannot be changed. Stratified randomization will be employed. Four stratification factors will be applied to achieve balanced randomization: 1) patient’s age, 2) gender, 3) Hunt & Hess grading and 4) the size of aneurysm.

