**Figure 1 F1:**
[figure not shown]
The study considerations of our trial.

This trial was elaborately designed to avoid several forms of bias and improve accuracy. The experience of presciously authors was noted and was merged into our design of the trial [19-21]. We will record all treatment results and surgical results, but only treatment results will be utilized for analysis. This will avoid selection bias, because all treatment results will include patients that may die from rebleeding, vasospasm or other complications, when awaiting surgery, especially those patients assigned to the intermediate or late surgery groups. Patients in intermediate or late surgery groups will receive emergency surgery when space-occupying hematoma, midline shift and emergency surgery indications are confirmed. Bias will be solved through the use of ITT analysis.

Although previous reports have demonstrated that patients in poor condition on admission within 6 hours after the onset of SAH achieved better outcomes than patients admitted later [12,26], this trial will enroll all the patients with PGASAH on admitted within 72 hours. As one of the largest hospitals in China, the number of patients admitted within 6 hours after the onset of SAH was relatively small in our department. More patients are transferred from other cities, even from the outlying areas in the west of China, and which takes time. The trial was not designed to include a small number of patients, but to include the overwhelming majority of the patients.

Neurosurgeon experience is an important factor in outcome after SAH. More than 4,000 surgeries are completed in our Department of Neurosurgery every year. Every neurosurgeon participating in the trial has accumulates experience of more than 200 neurosurgical clippings yearly, thus ensuring that every surgery will be performd to a high standard.

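### The 72-hour admission limit runs up to or past the close of the early-surgery window, so an eligible patient can be allocated to early surgery when it is no longer, or barely, possible

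*Protocol article*

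**What the plan says.** **Entry.** The Inclusion criteria set "No more than 72 hours from onset to admission". The Discussion repeats the limit: "this trial will enroll all the patients with PGASAH on admitted within 72 hours".

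**Early window.** The abstract (Methods/design) states: "The early surgery group received operation within 3 days after onset of subarachnoid hemorrhage (day of SAH = day 1". It then says that "the intermediate surgery group received operation from days 4 to 7". The Overview of study design gives the early window as "The early surgery group will receive operation within 3 days after onset of SAH", without the day-1 counting rule.

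**Allocation.** Under Randomization, every patient who meets the selection criteria is allocated by minimization to one of the three arms, and an allocation is final once made. One balancing factor is "4) the size of aneurysm", so the aneurysm must have been imaged before allocation. Neither the inclusion nor the exclusion criteria require the early window to be open at that moment.

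**Arrival.** The Discussion says that few patients reach the department within 6 hours, and adds: "More patients are transferred from other cities, even from the outlying areas in the west of China, and which takes time". It gives no distribution of arrival times.

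**Analysis.** Both intention-to-treat (ITT) and per-protocol (PP) analyses are planned.

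**The concern.** Timing of surgery is the only randomised factor, so each allocation should be deliverable when it is made. The entry limit and the early window are fixed separately, and the text does not line them up. A patient who arrives late but within the entry limit may already be on day 4, inside the intermediate window, and still be allocated to early surgery.

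Under ITT such a patient stays in the early arm but is operated on at a time that belongs to the intermediate arm. This narrows the contrast between early surgery and the other arms. If the PP set excludes patients operated on outside their window, it removes late arrivals from the early arm only, while similar patients remain in the other two arms. Late arrivals may differ in prognosis, so that comparison would no longer be protected by randomisation.

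**Working it through.** The plan gives no figure for this point, so the windows are compared first and a range is then computed under stated assumptions.

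**1. When the early window closes.** Let onset be at clock hour t (0 to 24) on day 1. Day 3 ends 72 − t hours after onset, that is, between 48 and 72 hours. Example: onset at 18:00 gives 72 − 18 = 54 hours. A patient admitted between 54 and 72 hours is eligible but already on day 4.

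**2. Chance of being past day 3, by admission time.** Assume t is uniform over the clock. For admission at a hours (48 ≤ a ≤ 72), the chance is (a − 48)/24: 25% at 54 h, 50% at 60 h, 75% at 66 h and 96% at 71 h.

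**3. Share of all entrants past day 3 at admission.** This is the average of step 2 over arrival times, which the article does not give. Three assumed patterns, each confined to 0–72 h:
- Uniform arrival: ∫ from 48 to 72 of (a − 48)/24 × (1/72) da = 12/72 = 16.7%.
- Truncated exponential with parameter m, density e^(−a/m) / [m(1 − e^(−72/m))]: 3.8% for m = 24 h and 0.5% (0.55%) for m = 12 h.

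Uniform arrival is the high end of this range.

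**4. Adding time from admission to surgery.** With an assumed 12 hours, the shares missing the day-3 window are 33.3%, 9.6% and 1.9% (uniform, m = 24, m = 12).

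**5. The alternative reading.** If the Overview means 72 elapsed hours, nobody admitted inside the limit is past the window at admission. With the same assumed 12 hours, patients admitted after hour 60 miss it: 12/72 = 16.7% (uniform), 3.4% (m = 24) and 0.4% (m = 12).

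**6. Dilution under ITT, using the step 3 shares.** Inputs from Sample size: unfavorable rate 50% and a difference of 30%, read as absolute, hence 50% versus 20%; two-sided 5%. With 88 patients in three equal arms (equal split assumed), 88/3 ≈ 29 per arm. Let q be the share of the early arm operated on after day 3, and assume the worst case that these patients have the full 50% rate. Then p_early = 0.20 + 0.30q and the difference is d = 0.30(1 − q).

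Power = Φ[(d − 1.96·se0)/se1], with se0 = √(2·p̄(1 − p̄)/n) and se1 = √([p1(1 − p1) + p2(1 − p2)]/n).

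- q = 0: se0 = √(2 × 0.35 × 0.65/29) = 0.1253; se1 = √(0.41/29) = 0.1189; Φ(0.458) = 68%.
- q = 16.7%: p_early = 0.25; se0 = 0.1271; se1 = 0.1228; Φ(0.007) = 50%.

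| Share past day 3 (q) | Difference | Power, 29 per arm | Power, 33 per arm (99/3) |
|---|---|---|---|
| 0 | 30.0 points | 68% | 73% |
| 0.5% | 29.8 points | 67% | 73% |
| 3.8% | 28.9 points | 64% | 70% |
| 16.7% | 25.0 points | 50% | 56% |

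The 68% at q = 0 is below the planned 80% for a separate reason: 50% versus 20% needs 39 per arm. Only the fall from the first row belongs to this point.

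**7. Sensitivity to the worst-case assumption.** If patients operated on after day 3 keep half the benefit, q = 16.7% gives d = 0.30 − 0.15 × 0.167 = 27.5 points and power of 59% at 29 per arm.

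**The case against.** Several stronger readings are tempting, and the documents do not support them.

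- **Some eligible patients can never receive early surgery.** This is literally true only under the abstract's day-1 rule. Read as 72 elapsed hours, the window is still open for anyone admitted before hour 72, and the difficulty is lack of time near the limit. That weakens the word never, but imaging, proxy consent and minimization still have to fit into what remains.
- **The trial loses 17% of its early arm and falls to 50% power.** That needs uniform arrival and complete loss of benefit at the day 3/4 boundary. The documents establish neither, and earlier arrival makes the effect negligible.
- **Late arrival is the rule at this site.** The Discussion says few arrive within 6 hours and that transfers take time. It does not say that most patients are transfers or that many arrive after 48 hours.
- **The emergency-surgery rule is a second contradiction.** The Discussion states openly: "Patients in intermediate or late surgery groups will receive emergency surgery when space-occupying hematoma, midline shift and emergency surgery indications are confirmed". This is a disclosed departure from allocation, which the article proposes to handle by ITT. It conflicts with no other statement. What is unclear is only whether patients who already meet it at randomisation are to be randomised.
- **Neither analysis can answer the timing question.** ITT still estimates the effect of assigned timing, in attenuated form. The PP criticism depends on a definition of the PP set that the article does not give.

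It can also be said that the 72-hour limit was chosen deliberately, to include most patients. The Discussion does defend recruiting beyond 6 hours. It does not address an entry limit that coincides with, or outlasts, the early window. Nor is this a detail lost in condensing the protocol: the entry limit and the arm windows are both stated, and they do not fit together.

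**Conclusion.** The point holds as an internal mismatch. Under the abstract's rule the early window closes up to 24 hours before the admission limit; under the elapsed-hours reading of the Overview the two coincide. Since allocation is open to all eligible patients and final, some can be assigned to an early window that is closed or nearly so. That follows from the article's own definitions and needs no assumption.

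The size does need assumptions and cannot be settled from the article. With onset uniform over the clock, the share past day 3 at admission runs from about 0.5% to 17%. Under the worst-case loss of benefit, the power lost at 29 per arm runs from under 1 percentage point to about 17 (67.7% to 50.3%). The effect may therefore be negligible or substantial. It deserves correction because it arises at randomisation and ITT cannot restore a contrast that was not delivered.

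**What to change.** 1. Define the early window once, on a single clock from onset, and use the same definition in the abstract, the Overview of study design and the Inclusion criteria. The present statements must be reconciled; the limits themselves are for the investigators to set.
2. Add a check at randomisation: a patient enters the three-arm allocation only if the early window is still open, with whatever allowance for preparation the investigators judge necessary.
3. State whether patients who already meet the emergency-surgery rule at randomisation are to be randomised. This is a clarification and a clinical decision for the investigators.

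**Cost.** An amendment and one check at randomisation. Some late arrivals would not enter the three-arm comparison, which may slow recruitment. They are not without value at present, since those allocated to intermediate or late surgery inform that comparison. Randomising late arrivals between those two arms only, and analysing them only there, would keep that information. It is optional: it complicates the minimization and makes the arms unequal in a trial of 99.
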